### 10.3 Population for Analysis

The following populations will be considered for the analyses:

- Intention to treat (ITT) population: All randomized participants, regardless of protocol adherence.
- Full Analysis Set (FAS): All randomized patients where a sealed facemask has been applied with the INOBlender set to 20 ppm at any point of time.
- Per Protocol (PP) set: All randomized patients who sufficiently comply with the protocol. Criteria for inclusion in the PP population will be specified in the statistical analysis plan, and the final criteria will be defined prior to database lock.
- Safety population: All randomized patients where a sealed facemask has been applied with the INOBlender set to 20 ppm at any point of time, i.e. identical to the FAS.

The primary analysis will be done on the Full Analysis Set.

### 10.4 Planned analyses

There will be one safety interim analysis in this trial, and one main efficacy analysis at the end of the trial. In addition, there will be a blinded evaluation of the variance in the primary endpoint after 20 patients.

- There will be a blinded evaluation of the variance in the primary endpoint after 20 patients, and a re-estimation of the sample size. The total sample size of the trial will be either the sample size calculated prior to the start of the trial, or the re-estimated sample size, whichever is largest. Thus, the total sample size will not be reduced due to the re-estimation.
- The safety interim analysis will be performed when approximately half of the patients have completed the intervention. This will thus occur when a minimum of 27 patients have completed the intervention. In case of an increased sample size due to the sample size re-estimation, the safety interim analysis will take place when approximately half of the patients in the (total) re-estimated sample size have completed the intervention. A separate document (the Data Monitoring Committee (DMC) charter) will detail the procedures for the interim analysis. A report will be written following the interim analysis, describing any deviations from the planned analysis, and a recommendation to either continue or stop the study. Treatment efficacy will not be investigated in the interim analysis.
- The final analysis will be performed when the planned number of patients (54, or the number of patients determined by the sample size re-estimation) have completed the intervention, and all data have been entered, verified and validated according to the data management plan.

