|   |                                                                                                                                                                                        | 2.2 Kidney function      | 2.2.1     | Increase in Serum urea concentration                          | Highest measured value up to day 28                                           |  |
|   |                                                                                                                                                                                        |                          | 2.2.2     | KDIGO AKI Stage up to day 28                                  | Kidney Disease Improving Global Outcomes acute kidney injury stage (1-3)      |  |
|   |                                                                                                                                                                                        | 2.3 Hemoglobin function  | 2.3.1     | Arterial MetHgb concentration                                 | Highest value during intervention or first sample after EOI                   |  |
|   |                                                                                                                                                                                        | 2.4 Platelet count       | 2.4.1     | Platelet count                                                | Lowest value up to 7 days                                                     |  |
|   |                                                                                                                                                                                        |                          |           |                                                               |                                                                               |  |
|   |                                                                                                                                                                                        |                          |           |                                                               |                                                                               |  |

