### 8.3 Time Period for Reporting AE and SAE

- For each patient the standard time period for collecting and recording AE will be from allocation and until End of Intervention
- For each patient the standard time period for collecting and recording SAE will be from allocation and until the 28 day follow up visit. At the 28 days visit an assessment will be made where we specifically ask for all SAEs mentioned in chapter 8.2. We will also assess discharge notes and treating physician for other events that fulfil the SAE definition and that can be assessed by the study team.
- For patients still admitted to hospitals at day 28 an effort will be made to secure access to main discharge note for assessment for any SAE that has occurred between day 28 and discharge.
- Any information that comes to investigators attention for any included patient prior to End of Trial will be assessed according to this protocol

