## **8.7 Data Monitoring Committee (DMC)**

A DMC will be recruited. Their work will be described in a charter based on the NORCRIN Standard Operating Procedure. This describes the roles and responsibilities of the DMC, including the timing of meetings, methods of providing information to and from the DMC, frequency and format of meetings, statistical issues and relationships with other Sponsor. The charter and the DMC should be in place before the first patient is included.

The DMC will meet after the interim analysis, and in the event of SUSAR reporting.

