## 10 STATISTICAL METHODS AND DATA ANALYSIS

### 10.1 Determination of Sample Size

One previous study in a different setting has shown that 71% of patients respond to the treatment with an absolute increase in SpO2 of >5 percentage points(21). We assume a standard deviation of 10 percentage points, and a within subject correlation of 0.8 based on clinical experience. This implies a standard deviation of the change in SpO2 (before minus after intervention) of 6.32%. A difference in improvement in SpO2 of 5 percentage points between the intervention groups is considered clinically significant. To identify a difference of improvement of SpO2 of 5 percentage points, with a power of 80%, we need to include 54 patients (27 in each arm) in this trial, using a significance level of 5%. Because of the uncertainty related in the magnitude of the variance in the SpO2 change, a simple blind re-estimation of the sample size based on the variance from a subsample of the 20 first patients will be done. The sample size will be adjusted if necessary, but the total sample will not be reduced (to less than 54). By using a blinded one-sample variance estimator for sample size recalculation, the effect of sample size adjusting on the type I error rate is negligible and no additional measures are needed to control the significance level(22).

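### Section 10.4 lets the blinded variance of the SpO2 change postpone the only scheduled DMC safety look, although no efficacy is tested there

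*Protocol*

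**What the plan says.** Protocol 10.4 provides for one safety interim, at roughly half of the patients and not before 27 have finished the intervention. It also provides for a blinded variance review after 20 patients that can raise the total above 54 but not lower it. If the total rises, "the safety interim analysis will take place when approximately half of the patients in the (total) re-estimated sample size have completed the intervention". The same section states that efficacy is not looked at in this interim and leaves its procedures to the DMC charter. No upper limit on the re-estimated total appears in 10.1 or 10.4.

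On meetings, 8.7 says: "The DMC will meet after the interim analysis, and in the event of SUSAR reporting". The charter, which is not part of the document at hand, is to cover the timing and frequency of meetings.

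Section 8.2.2 lists serious events expected in this population, among them cardiac arrest, bradycardia, renal failure, brain hypoxia and acute hypotension. These go into the CRF but are not reported to the sponsor. Suspected rebound reactions and deaths before end of intervention always are, and 8.5 requires unexpected SAEs to be reported within 24 hours.

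The intervention is estimated at one hour (section 3), while SAE collection runs to day 28: "At the 28 days visit an assessment will be made where we specifically ask for all SAEs mentioned in chapter 8.2" (8.3). The kidney endpoint in section 2 is "KDIGO AKI Stage up to day 28".

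**The concern.** An interim that tests efficacy is tied to a fraction of the final sample because its boundary depends on the information accrued. A look at safety alone has no such constraint. Its purpose is to show the DMC a comparison of harms by arm after a tolerable number of patients have been exposed, and that number does not depend on how variable SpO2 is. Under 10.4, a noisier SpO2 change puts off the first such comparison.

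Section 7.3 names DMC monitoring among its mitigations of risk, and 12.3 has patients treated before any consent. Section 1.2.2 reports that a meta-analysis found significantly more renal failure with inhaled nitric oxide, and notes that the product characteristics do not list it. Renal failure is on the 8.2.2 list, so an excess in one arm may not bring the DMC together before the scheduled look.

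**Working it through.** **Inputs (Protocol 10.1).** The assumptions are: "We assume a standard deviation of 10 percentage points, and a within subject correlation of 0.8 based on clinical experience". The target is a difference "of 5 percentage points between the intervention groups is considered clinically significant". Power is 80% and the significance level 5%, taken as two-sided because a one-sided calculation gives 40 patients and does not match the stated total. Allocation is 1:1 (10.2).

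**Reproducing the stated size.** SD of change = √(2 × 10² × (1 − 0.8)) = √40 = 6.32. A two-sample t-test for a difference of 5 then needs 27 per arm, or 54 in all (power 81.3%). The normal approximation gives 26 per arm. The protocol's 54 is confirmed, and half of it is 27.

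**How far the look moves.** The rule amounts to max(54, re-estimated N) ÷ 2. With the same t-test:

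| SD of change | Total N | Safety look at |
|---|---|---|
| 6.32 | 54 | 27 |
| 7 | 64 | 32 |
| 8 | 84 | 42 |
| 9 | 104 | 52 |
| 10 | 128 | 64 |

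An SD of 10 corresponds to a within-subject correlation of 0.5 instead of 0.8: √(2 × 10² × 0.5) = 10. For the look to fall after more than 54 patients, the total must exceed 108, which needs an SD of about 9.2.

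**How likely a shift is if the planned SD is right.** I simulated at least 20,000 trials with a true SD of 6.32, taking the one-sample SD of the first 20 patients (10 per arm) and recomputing N:

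| True effect | N raised above 54 | Median look | 90th percentile look | Look after more than 54 patients |
|---|---|---|---|---|
| 0 | about 41% | 27 | 37 | about 0.4% |
| 5 points | about 59% | 30 | 43 | about 1.5% |

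The one-sample estimator absorbs part of the treatment effect, so an increase is more likely when the drug works as assumed.

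**Calendar time.** Section 3 gives a 24-month recruitment period but dates that span 12 months, so both are used, assuming even accrual of 54 patients. A look at 27 comes at month 12 (or 6). At SD 8 the look at 42 comes at 42 ÷ (54 ÷ 24) = month 18.7 (or 9.3).

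**Follow-up at the trigger.** Under the same accrual, patients enrolled within the last 28 days number 54 × 28 ÷ 730 = 2.1 (24 months) or 54 × 28 ÷ 365 = 4.1 (12 months). About 2 to 4 of the first 27, or 8% to 15%, would not have reached day 28. Clustered enrolment would raise this.

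**The case against.** A safety look at half of the sample is a conventional choice, and 10.4 and 8.7 do not contradict each other. The charter may add meetings or specify the data cut. Oversight also does not rest on this look alone: deaths before end of intervention, suspected rebound reactions and unexpected SAEs reach the sponsor; an annual safety report is due (8.5.2); and the trial may be stopped for medical or ethical reasons (6.3). All of this stands and limits the size of the point. None of it gives the DMC a comparison by arm, and because 10.4 itself fixes when the interim occurs, the correction belongs there.

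Three stronger readings are tempting and are not supported.

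- A reader might infer that more patients than the whole planned trial will probably be treated before the DMC looks. At the planned SD the chance is about 0.4% to 1.5%. It becomes a real prospect only if that SD is badly wrong.
- A reader might infer that events on the 8.2.2 list can never be SUSARs. Section 8.1.4 does not say which list decides expectedness, 8.2.1 gives a separate list for inhaled nitric oxide that omits cardiac arrest and renal failure, and the flow chart in 8.5 is not shown. The SUSAR route for these events is doubtful, not excluded.
- A reader might infer that the look would be largely empty of safety data and should wait for day 28. Under even accrual only about 2 to 4 of 27 patients lack day-28 follow-up. Cardiac arrest during the intervention comes from the treatment CRF, and heart rate and blood pressure from the monitor (9.2). Waiting would also add to the delay.

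**Conclusion.** The point holds as a matter of timing. Section 10.4 makes the only scheduled DMC safety look depend on the variance of an efficacy endpoint, with no stated cap and no statistical reason for the link. If the planned SD is correct, the usual effect is modest: a median look at 27 to 30 patients and a 90th percentile of 37 to 43. If the SD of change is 8 to 10, the look falls at 42 to 64 patients. Section 10.1 itself calls this variance uncertain. Incomplete day-28 data are a secondary matter that clear reporting can handle. The figures rest on a two-sided 5% test, normally distributed changes, 20 patients split evenly in the variance review and, for the calendar and follow-up figures, even accrual. The conclusion that this is the only scheduled look rests on the protocol text; the charter has not been seen.

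**What to change.** In 10.4, hold the first DMC safety look when 27 patients have completed the intervention, whatever the re-estimation gives. If the total is raised, add a second look at half of the new total. State the same triggers in 8.7 and carry them into the charter.

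Specify that the report uses all data available at the cut, including day-28 data for patients who have reached it, and shows follow-up status by arm. The look should not be delayed to complete follow-up.

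The cost is a change of wording and, only if the sample is enlarged, one extra DMC report. No efficacy test is made, so there is no alpha cost.

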## 10.5 Statistical Analysis

Demographics and other baseline characteristics, such as age, gender etc., will be described for all randomized patients (the ITT population). Continuous variables will be described in terms of number of observations (n), mean value and standard deviation. All variables of a categorical nature will be displayed with frequencies and percentages. The tabulation of the descriptive statistics will be split by treatment group.

The primary efficacy endpoint, the difference in the change in SpO2 from before to after the intervention, will be analyzed using a linear regression model where the intervention variable will be adjusted by the baseline SpO2 and the stratification variable used in the randomization (study site). Currently there are two sites in this trial. If additional sites are added during the trial, these will represent additional strata. If the residuals from the regression model is not normally distributed, suitable transformations will be applied to the data or non-parametric alternatives will be used.

For the primary endpoint, a subgroup analysis will be performed according to later confirmed Covid-19 status of the patients. Presence of COVID-19 disease is classified as per WHO definition of confirmed COVID-19 (see ch 1.1.1), and with the SARS-CoV-2 test routine used at the given point of time in the respective institution. Data will be extracted from the EPJ on the 28-day visit.

Analyses of secondary endpoints will be performed in a similar manner as for the primary endpoint and/or using repeated measures mixed models for continuous variables, and logistic regression models for binary endpoints. Subgroup analyses will be performed according to later confirmed Covid-19 diagnosis for the secondary endpoints related to SpO2 (endpoints 1.2.1-1.2.4).

The primary and secondary analyses will be performed in the FAS, and robustness analyses will be performed in the PP population. A separate statistical analysis plan (SAP) will provide further details on the planned statistical analyses. The SAP will be finalized, signed and dated prior to database lock. The treatment allocation will be revealed after the database lock and used in the statistical analysis.

Deviation from the original statistical plan will be described and justified in the Clinical Study Report.

Amendments to plan can be done until day of database (DB) lock.

## 11 STUDY MANAGEMENT

### 11.1 Trial Master File (TMF)

A paper- based Trial Master File will be kept at the Air Ambulance Base at Lørenskog, with Invest Site Files at participating departments. These will be based on NorCrin SOP. This will made available to monitor and authorities upon request.

### 11.2 Investigator Delegation Procedure

The principal investigator is responsible for making and updating a “delegation of tasks” listing all the involved co-workers and their role in the project. He will ensure that appropriate training relevant to the study is given to all of these staff, and that any new information of relevance to the performance of this study is forwarded to the staff involved. A delegation log will be produced and stored in the TMF.

### **11.3 Protocol Adherence**

Investigators ascertain they will apply due diligence to avoid protocol deviations.

All significant protocol deviations will be recorded and reported in the Clinical Study Report (CSR)

### **11.4 Study Amendments**

If it is necessary for the study protocol to be amended, the amendment and/or a new version of the study protocol (Amended Protocol) must be notified to and approved by the Competent Authority and the Ethics Committee according to EU and national regulations.

### **11.5 Audit and Inspections**

Authorized representatives of a Competent Authority and Ethics Committee may visit the center to perform inspections, including source data verification. Likewise, the representatives from sponsor may visit the center to perform an audit. The purpose of an audit or inspection is to systematically and independently examine all study-related activities and documents to determine whether these activities were conducted, and data were recorded, analyzed, and accurately reported according to the protocol, Good Clinical Practice (ICH GCP), and any applicable regulatory requirements. The principal investigator will ensure that the inspectors and auditors will be provided with access to source data/documents.

## **12 ETHICAL AND REGULATORY REQUIREMENTS**

The study will be conducted in accordance with ethical principles that have their origin in the Declaration of Helsinki and are consistent with ICH/Good Clinical Practice and applicable regulatory requirements.

Registration of patient data will be carried out in accordance with national personal data laws.

### **12.1 Ethics Committee Approval**

The study protocol, including the patient information and informed consent form to be used, must be approved by the regional Ethics Committee before enrolment of any patients into the study.

The investigator is responsible for informing the Ethics Committee of any serious and unexpected adverse events and/or major amendments to the protocol as per national requirements.

### **12.2 Other Regulatory Approvals**

The protocol will be submitted and approved by the Norwegian Medicines Agency prior to study start.

### **12.3 Informed Consent Procedure**

The inclusion criteria in this study is hypoxia to an extent representing a severe medical condition. Therefore, at the time of inclusion, the patient is neither competent to consent, nor able to receive any information about the study. The clinical setting in which the study is performed is by nature a situation where consent prior to inclusion and treatment is not possible to obtain. It would also be ethical questionable to trust that any

information would be received and processed by the patient. Therefore, the study participants or next of kin will be informed and asked to participate post treatment. The informed consent procedure is as follows:

- Inclusion, treatment and data recording will occur before any informed consent is obtained
- After hospitalization, and within the 28 days to follow-up, either the patient (if deemed competent) or the next of kin will be informed with written information (see patient consent form) and asked to participate
- The consent will be for storing, analyzing and publish data collated in the CRF (treatment is already administered)
- If the consent is given by next of kin of a deceased patient, or a patient deemed to not recover to consent competency, the consent from next of kin is considered to be final
- If the consent is given by next of kin of a patient suspected to recover from incompetency, the consent from the patient will be obtained after recovery
- Information about the study and consent is given both oral (study personnel) and written (Patient consent form)
- Consent is written (patient consent form). Oral consent can be obtained but require signature from two health care personnel (of which one study personnel/ investigator) stating that the patient has consented.

[figure not shown]

Patient consent procedure

## 12.4 Subject Identification

The investigator is responsible for keeping a list of all patients (who have received study treatment or undergone any study specific procedure) including patient's date of birth, personal number and full names in a code list approved storage at site for such information.

The patients will be identified in the CRFs by their three-digit randomization number.

## 13 TRIAL SPONSORSHIP, OWNERSHIP AND FINANCING

Oslo University Hospital retains full ownership to all data and results generated in this trial, and it is the sole financial sponsor. Further funding may be sought during the trial period. Several of the investigators are partly

employed by the Norwegian Air Ambulance Foundation. This foundation has had no place in the design or ownership in this trial.

## **14 TRIAL INSURANCE**

The Principal investigator will obtain insurance coverage for this study through membership of the Drug Liability Association, and ensure proof of membership is sent Competent Authority and stored in the TMF prior to inclusion of the first patient.

